## Abstract

**Background:**

Postoperative cognitive dysfunction (POCD) is a common complication of cardiac surgery. Studies have identified potentially injurious roles for cardiopulmonary bypass (CPB) and subsequent reperfusion injury. Cognitive dysfunction has also been linked to the deleterious effects of hyperoxia following ischemia-reperfusion injuries in several disease states, but there has been surprisingly little study into the role of hyperoxia in reperfusion injury after CPB. The potential for tightly regulated intraoperative normoxia to ameliorate the neurocognitive decline following cardiac surgery has not been investigated in a prospective manner. We hypothesize that the use of a protocolized management strategy aimed towards maintenance of an intraoperative normoxic level of oxygen, as opposed to hyperoxia, will reduce the incidence of POCD in older patients undergoing cardiac surgery.

**Methods/Design:**

One hundred patients aged 65 years and older undergoing non-emergency coronary artery bypass grafting surgery on cardiopulmonary bypass will be enrolled in this prospective, randomized, controlled trial. Subjects will be randomized to receive a fraction of inspired oxygen of either 35% or 100% while under general anesthesia throughout the intraoperative period. The primary outcome measure will be the incidence of POCD in the acute postoperative phase and up to 6 months. The assessment of neurocognition will be undertaken by trained personnel, blinded to study group, with the telephone Montreal Cognitive Assessment (t-MoCA) tool. Secondary outcome measures will include assessment of delirium using the Confusion Assessment Method (CAM and CAM-ICU), as well as time to extubation, days of mechanical ventilation, length of ICU and hospital stay and mortality at 6 months. With the aim of later identifying mechanistic aspects of the effect of oxygen tension, blood, urine, and atrial tissue specimens will be taken at various time points during the perioperative period and later analyzed.

**Discussion:**

This trial will be one of the first randomized controlled studies to prospectively assess the relationship between intraoperative oxygen levels and postoperative neurocognition in cardiac surgery. It addresses a promising biological avenue of intervention in this vulnerable aging population.

**Trial registration:**

ClinicalTrials.gov Identifier: NCT02591589, registered February 13, 2015.

**Electronic supplementary material:**

The online version of this article (doi:10.1186/s13063-017-2337-1) contains supplementary material, which is available to authorized users.

## Background

There are approximately 300,000 cardiac surgical procedures annually utilizing cardiopulmonary bypass (CPB) in the United States alone [1]. Postoperative cognitive dysfunction (POCD) remains a common adverse outcome in patients undergoing cardiac surgery, and has been reported to occur in up to 50% of patients after coronary artery bypass grafting (CABG) at the time of hospital discharge. Defined by deficits in working memory and executive function, this condition persists in as many as 30% of patients at 6 months [2]. A related cognitive disorder, postoperative delirium, also occurs frequently in this population. While often minimized due to its apparent temporary nature, recent data have demonstrated that postoperative delirium has lasting effects, with decreased cognitive performance up to 1 year after surgery and an accelerated rate of age-related cognitive decline compared to patients without delirium [3]. Despite the seemingly minor and temporary effects these cognitive deficits may seem to pose to the physical recovery of the cardiac surgical patient, data suggest that patients who suffer from these conditions display a higher rate of overall mortality [4]. Hence, postoperative delirium and POCD following cardiac surgery is a considerable problem, perhaps the most frequently encountered adverse complication following cardiac surgery [5]. The incidence of neurological sequelae after cardiac surgery is only expected to increase as surgery continues to be performed on an ever-aging population [6].

The delivery of oxygen has long been a cornerstone of anesthesia practice, traditionally with titration of oxygen therapy to ensure avoidance of potentially injurious periods of hypoxemia. However, the same attention has not been afforded for levels of relative hyperoxemia, presuming that excess oxygen is relatively harmless. Emerging clinical data within a variety of arenas suggest that this assumption may not be true. There appears to be potentially deleterious effects from hyperoxemia, whether it be demonstration of extension of infarct size post myocardial infarction [7], worse neurological outcomes and higher mortality in patients receiving therapeutic hypothermia following return of spontaneous circulation (ROSC) after cardiac arrest [8], or higher mortality in the intensive care unit [9]. Given these data, recent investigation has focused on assessment of potentially detrimental consequences of hyperoxemia in the domain of CPB during cardiac surgery [10, 11]. However, the potential for tightly regulated intraoperative normoxia to ameliorate POCD following cardiac surgery has not been investigated in a prospective manner [12, 13].

The objective of this trial is to determine whether patients undergoing CABG on CPB maintained under normoxic conditions throughout the intraoperative period will have a lower incidence of POCD and delirium than those exposed to hyperoxia. Given the disease burden, investigation into such a mechanistically intuitive and potentially simple intervention could impact hundreds of thousands of cardiac surgery patients a year.

## Methods/design

### Study design

To assess the relationship between intraoperative arterial partial pressure of oxygen (PaO_2_) and the incidence of POCD and delirium we have designed a single-center, randomized, double-blind superiority trial of 100 participants with an allocation of 1:1. Subjects undergoing CABG surgery with CPB will be prospectively randomized to one of two different levels of fraction of inspired oxygen (FiO_2_) intraoperatively. The primary outcome of postoperative cognitive decline will be assessed via cognitive testing at baseline, daily from postoperative day 1 until hospital discharge, and then by phone at 1, 3, and 6 months postoperatively (Fig. 1 for trial schematic). Table 1 details the structured study summary according to the World Health Organization Trial Registration Data Set. The trial protocol was written in accordance with the Standard Protocol Items: Recommendations for Interventional Trials (SPIRIT) checklist [14] (Additional file 1).

**Fig. 1 Fig1:**
[figure not shown]
Study schema

**Table 1 Tab1:** WHO Trial Registration Data Set - Structured Summary

Data category	Information
Primary registry, trial identifying number	Clinicaltrials.gov Identifier - NCT02591589
Date of registration in primary registry	February 13, 2015
Secondary identifying numbers	
Sources of monetary support	Foundation for Anesthesia Education and Research Mentored Training Research Grant
Contact for public queries	SS, Department of Anesthesia, Beth Israel Deaconess Medical Center, Boston MA, USA
Contact for scientific queries	SS, Department of Anesthesia, Beth Israel Deaconess Medical Center, Boston MA, USA
Public title	Intraoperative Oxygen Concentration and Neurocognition After Cardiac Surgery
Scientific title	The relationship between administered oxygen levels and arterial partial oxygen pressure to neurocognition in cardiac surgical patients
Country of recruitment	USA
Health problem under investigation	Neurocognition after cardiac surgery
Key inclusion and exclusion criteria	Age ≥ 65 years, elective or urgent coronary artery bypass surgery (CABG) on cardiopulmonary bypass (CPB)
Study type	Interventional Allocation: randomized Interventional model: Masking: blinding of participant and outcomes assessor
Date of first enrollment	September 2015
Target sample size	100
Recruitment status	Recruiting as of January 2017
Primary outcome	Change in Telephonic Montreal Cognitive Assessment from baseline up to 6 months
Key secondary outcomes	Delirium incidence, time to extubation, Acute kidney injury incidence

The SPIRIT figure (Fig. 2) demonstrates the schedule of enrollment, interventions, and instruments of assessment used in the trial.

**Fig. 2 Fig2:**
[figure not shown]
Standard Protocols Items: Recommendations for Interventional Trials (SPIRIT) figure

### Study setting

Beth Israel Deaconess Medical Center (BIDMC) is a 700-bed tertiary care academic facility and Harvard Medical School teaching hospital. More than 900 open-heart procedures are performed on an annual basis, of which approximately 400 of these are CABG surgeries with CPB.

### Study registration

The study will be conducted in accordance with the ethical principles taken from the Declaration of Helsinki and adhere to the principles of Good Clinical Practice. The Committee on Clinical Investigations Institutional Review Board at Beth Israel Deaconess Medical Center approved the study protocol and provides ongoing oversight (IRB Protocol Number 2014-P-000398). Upon completion the trial will be reported in adherence to the Consolidated Standards of Reporting Trials (CONSORT) guidelines [15] in addition to the Standard Protocols Items: Recommendations for Interventional Trials (SPIRIT) checklist [14]. This study was registered at the U.S. National Institutes of Health with ClinicalTrials.gov on 13 February 2015 and carries the trial identification number NCT02591589. The trial is ongoing and currently recruiting. All amendments to the protocol are reported to the Institutional Review Board for approval.

### Inclusion and exclusion criteria

The study will enroll adult patients aged 65 or older undergoing elective or urgent on-bypass CABG cardiac surgery with subsequent admission to a cardiovascular intensive care unit (ICU). Patients undergoing emergent CABG surgery, combined CABG and other cardiac procedures, procedures requiring single lung ventilation, off-pump cardiac bypass surgery, or patients with signs of cardiogenic shock as dictated by preoperative inotropic, intra-aortic balloon counterpulsation or mechanical circulatory support devices will be excluded. Patients with evidence of severe cognitive impairment at baseline, as defined by a Telephone Montreal Cognitive Assessment (t-MoCA) score below 10, will also be excluded.

### Intervention and anesthesia regimen

Patients will be randomized on a 1:1 basis through a block randomization schedule using sealed envelopes to one of two experimental groups based on arterial oxygen tensions. In the first group, the FiO_2_ will be set at a minimum of 0.35 to maintain their PaO_2_ above 70 mmHg or oxygen saturations (SpO_2_) greater than or equal to 92%, and if necessary, titrated up to prevent potentially injurious hypoxemia (SpO_2_ < 92%). During CPB a blended air/oxygen mixture will be titrated to arterial blood gas analysis with aim of maintenance of PaO_2_ between 100 and 150 mmHg. This intervention group will be termed the normoxic arm.

The second arm of this trial will consist of subjects exposed to an FiO_2_ set at 1.0 throughout the intraoperative period, including during cardiopulmonary bypass. PaO_2_ will be measured periodically; however, it will not be used to titrate FiO_2_. This control group will be termed the hyperoxic arm.

Anesthetic regimen will not be standardized but is instead at the discretion of the treating provider. To standardize other key aspects of ventilator support in line with current best practice, mechanical ventilation will be performed according to a protocol based on current institutional standard of care. Tidal volumes will be set to 6–8 cc/kg and positive end-expiratory pressure (PEEP) levels of 0–5 cm H_2_O in both groups, with flexibility for provider preference. Study ventilator settings will be applied after induction of general anesthesia and successful endotracheal intubation and continued throughout the surgery, until surgical closure. Blood gas analysis and recording will be performed in both groups in the same manner as in the course of normal clinical care. Intraoperative FiO_2_, arterial oxygen saturation, mean arterial pressure, tidal volume, PEEP, and temperature will be extracted from the anesthesia record at 30-second intervals.

### Safety assessments and blinding

The Principal Investigator and other physician co-investigators will be in communication with the clinical team throughout the intra-operative period to ensure protocol adherence. Further criteria for withdrawal from the study preoperatively include active ongoing cardiac ischemia or acute decompensated arrhythmia, low oxygen saturation (SpO_2_ < 90%) on supplemental oxygen, or the use of continuous vasopressor or inotrope infusion medications. Patients will be withdrawn intraoperatively if they develop significant hemodynamic compromise because of cardiac surgery or sustained intra-operative oxygen desaturation (SpO_2_ < 90% for more than 3 minutes). At any time during the perioperative period patients may be withdrawn for significant physician or nursing concern.

Because real-time monitoring of protocol compliance requires knowledge of the patient’s assigned treatment, the study team utilizes a coordinated team approach. For every case, the study team members assessing the primary and secondary outcomes of the study will be blinded to the group assignment. This includes research staff administering neurocognitive assessments as well as physician staff monitoring patient progress and safety. The physician principal investigator is unblinded, and is responsible for conveying the treatment assignment to the clinical team and monitoring compliance with the assigned regimen intraoperatively. A trials specialist within the research group will monitor protocol compliance, occurrence and report any adverse events to the institutional review board (IRB).

## Study outcomes and their measurement

### Primary endpoint

To assess the occurrence of POCD we will use the t-MoCA. Scores on the t-MoCA will be measured preoperatively and postoperatively, using a daily in-hospital assessment until discharge or 30 days, whichever is sooner. In order to reduce fatigue completing assessments, if t-MoCA scores have plateaued for three consecutive days and CAM assessments are negative, assessments will occur every third day in-hospital through a skip pattern algorithm.

The t-MOCA is an adaptation of the widely used MoCA assessment [16], with items requiring writing and picture recognition removed. T-MoCA results in a 22-point scale and has been validated as a marker for cognitive function [16, 17]. Additionally, there will be telephone follow-up and t-MOCA assessment at 1, 3, and 6 months postoperatively, which does not require that participants be assessed in person. The telephonic version of the MoCA was chosen as the cognitive test to be performed both in-person and in telephonic follow-up so as to have equivalent scoring between assessments at all follow-up time points throughout the study. In previous studies, testing to 6 months has been shown to accurately reflect longitudinal follow-up of cognitive trajectories after CABG [18, 19] and thus this was the time endpoint for the follow-up in our study. Blinded, specially trained study staff will administer the assessments and assist in data collection.

### Secondary endpoints

The Confusion Assessment Method (CAM), which is a diagnostic algorithm for delirium, will be administered simultaneously with the t-MoCA postoperatively, as there are data to support a more pronounced reduction in cognitive ability in patients exhibiting postoperative delirium. This will assess for differential incidences of postoperative delirium that may occur between groups as a secondary endpoint. While patients are in the ICU and non-verbal, the t-MoCA will not be assessed and the validated CAM-ICU test for the incidence of delirium will be used in place of the CAM [19, 20]. Other secondary outcomes to be measured will include the time to extubation, days of mechanical ventilation, length of ICU and hospital stay, patient mortality at 30 days and 6 months. Other postoperative events as collated and reported in the Society of Thoracic Surgeons (STS) database will be reported and assessed including renal failure, stroke, myocardial infarction, reoperation, and sternal wound infection.

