## Statistical analysis

### Sample size calculation

Using previous data [3], and assuming a cross walk between t-MoCA and Mini-Mental State Examination (MMSE) [22], a two-sided α = 0.05 and 80% power, we will need 74 subjects in total to detect a mean difference in t-MoCA scores of 2 (standard deviation of 3) between the hyperoxia and normoxia group at postoperative day 2. This cognitive decrement was previously reported as clinically significant and postoperative day 2 was reported as the in-hospital postoperative nadir time point [19]. A total of 100 randomized subjects who have undergone the entire intraoperative intervention will be enrolled to allow for potential attrition from loss to follow-up or withdrawal.

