### Data analysis

Descriptive statistics of the data will be performed. Continuous data will be represented using mean (± standard deviation) or median (interquartile range) for variables not normally distributed and compared using parametric or non-parametric *t* tests as appropriate. Categorical data will be presented using proportions and compared using a chi-square (or Fisher’s exact) test. Two-sided *p* values less than 0.05 will be considered statistically significant. All analyses will be conducted using the intention-to-treat principle. No interim analyses are planned and there are no stopping rules for this trial. SAS 9.3 (SAS Institute, Cary, NC, USA) will be used for all analyses.

The primary outcome of the study is t-MoCA trajectories (values of t-MoCA) at postoperative day 2 between the two groups. An unadjusted *t* test (or non-parametric equivalent) will be used to assess superiority. Linear regression will be performed to identify independent predictors of t-MoCA as well as changes in t-MoCA over the 6-month study period. To account for the multiple measurements per subject, we will employ repeated measures regression techniques. Due to flexibility of timing of patient interviews, possibility of censored data and repeated observations, secondary analysis would require the use of a piecewise mixed-effects linear regression model measurement. Interaction will be assessed in the mixed-effects model to test if the t-MoCA slopes are different between groups.

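### Four recovery durations fall under a general test that takes no account of death, so an early death counts as a short, favourable duration; the effect is small and cheap to remove

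*Protocol article*

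**What the plan says.** The Secondary endpoints section lists "time to extubation, days of mechanical ventilation, length of ICU and hospital stay, patient mortality at 30 days and 6 months". The Abstract has nearly the same list: "time to extubation, days of mechanical ventilation, length of ICU and hospital stay and mortality at 6 months". In both places the four durations are plain lengths of time, and mortality is a separate outcome. Table 1 (WHO Trial Registration Data Set) gives the key secondary outcomes as "Delirium incidence, time to extubation, Acute kidney injury incidence", so time to extubation is one of the three singled out.

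Under Data analysis, continuous variables are summarised by mean or median and "compared using parametric or non-parametric *t* tests as appropriate". The same section states: "All analyses will be conducted using the intention-to-treat principle". Censoring appears once, in the reasons for the longitudinal t-MoCA model: "possibility of censored data and repeated observations, secondary analysis would require the use of a piecewise mixed-effects linear regression model". The text that follows assigns models to adverse events, ADL, GDS and biomarkers, but none to the four durations.

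**The concern.** Death ends all four durations. A patient who dies ventilated on day 1 has about one ventilator day and one ICU day, among the shortest values in the trial. Taken at face value, the comparison reads this as a good recovery. The same patient has no extubation time. Either the patient is left out, which sits badly with intention to treat, or some value is chosen later.

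If one arm had more early deaths, that arm would tend to look as though its patients left the ventilator, the ICU and the hospital sooner. Reporting mortality beside the durations tells the reader about the deaths but does not correct the duration comparisons. At stake are four secondary outcomes, one of them labelled key. The primary outcome, t-MoCA at postoperative day 2, is not involved.

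**Working it through.** **The plan's own figure.** No sample size is stated for the durations. The one that is stated, 74 in total for a t-MoCA difference of 2 with SD 3, reproduces. The normal approximation gives 2 × (1.96 + 0.84)² × 3² / 2² ≈ 35.3, so 36 per arm and 72 in total. The t-based calculation gives 36.3, so 37 per arm and 74. Nothing below changes it.

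**Which rule applies.** The durations are continuous and no section gives them a model of their own, so the general rule is the only one that reaches them. The article mentions no ventilator-free days, no rank for death, no competing event and no value for a patient never extubated.

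**Effect of one early death on the rank test.**
- Inputs: 100 patients allocated 1:1 (Study design), taken as n1 = n2 = 50.
- Null standard error of P(X>Y): √[(n1 + n2 + 1) / (12·n1·n2)] = √(101 / 30,000) = 0.058.
- One patient is compared with 50 in the other arm, out of 50 × 50 = 2,500 pairs. Going from shortest to longest changes P(X>Y) by 50 / 2,500 = 0.02, and 0.02 / 0.058 = 0.34 SE. This is the full swing between best-rank and worst-rank coding.
- Against a neutral mid-rank the change is half of that: 25 / 2,500 = 0.01, and 0.01 / 0.058 = 0.17 SE. This measures how far the plain coding pulls the result.

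**How many patients.** The article gives no mortality rate, so this is an assumption.

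| Assumed mortality | Expected deaths in 100 | Chance of at least one |
|---|---|---|
| 1% | 1 | 63% |
| 2% | 2 | 87% |
| 3% | 3 | 95% |

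If three deaths were all early and all in one arm, the pull from mid-rank would be 3 × 0.01 = 0.03, or about 0.52 SE. Significance at two-sided 0.05 needs 1.96 SE.

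**Direction and size on the time scale.** Assumptions, none from the article: hospital stay log-normal with median 7 days and log-SD 0.4 in both arms, every death recorded as 1 day, 50 per arm, Mann-Whitney test, 4,000 simulated trials per scenario.

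| Mortality, arm A v arm B | Mean stay, B minus A (days) | Significant, plain durations | Significant, death ranked worst |
|---|---|---|---|
| 2% v 2% | 0.04 | 4.4% | 4.7% |
| 2% v 6% | −0.26 | 6.0% | 6.5% |
| 2% v 10% | −0.53 | 10.7% | 10.8% |
| 2% v 20% | −1.18 | 33% | 35% |

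Arithmetic agrees. Mean stay in survivors is 7 × exp(0.4² / 2) = 7.58 days, so each death at 1 day removes 6.58 days. An excess of 4 percentage points removes 0.04 × 6.58 = 0.26 day. The rejection rates are alike under the two codings, but the direction is opposite: plain durations favour the arm with more deaths, and worst-rank coding counts against it. With equal mortality the plain test keeps its size.

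**The case against.** The strongest reply is that this is unstated detail and not an error. A journal article condenses a fuller protocol, and an analysis plan may say how deaths are coded. The general rule never names the durations and leaves the choice of test open, and worst-rank coding would be compatible with it. Nowhere does the article say that a death scores one day or that a patient never extubated is dropped. A reader might infer that it adopts those scorings; it does not. They are what the stated rule yields if nothing is added. That still makes this more than a gap, because the default result points the wrong way for the patients who did worst.

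Three further limits stand.
- Few early deaths are likely. Emergency and combined surgery and cardiogenic shock are excluded, and the 100 are to be patients who completed the intraoperative intervention.
- Only a death earlier than a typical extubation or discharge reverses the scale. A patient who dies after a long ventilator course already has a long, unfavourable value.
- Plain durations with mortality alongside are a recognisable choice, and ranking death worst turns a duration into a composite. That is a real cost, but it does not make the plain comparison read correctly when early deaths differ.

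**Conclusion.** The point holds as a modest one. As the article stands, the four durations fall under a test that ignores death: an early death looks like a fast recovery, and a death before extubation leaves no extubation time. The pull is up to about 0.17 SE per excess early death against a neutral mid-rank, with 50 per arm. At an assumed 1–3% mortality, only about 1 to 3 patients at most are expected to be affected. It matters only if early deaths differ between arms, and the primary outcome and sample size are unaffected.

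Two stronger readings should be resisted. A reader might take 0.34 SE per death, or 0.69 SE for two, as the bias; that is the swing between the two extreme codings, twice the distance from a neutral rank. A reader might also take the Background's link between cognitive complications and higher mortality as a sign of unequal early deaths. That link concerns overall mortality in patients with those conditions and says nothing about early deaths by oxygen arm.

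**What to change.** State, for time to extubation, ventilator days, ICU stay and hospital stay, that death before extubation or discharge takes the worst rank. Compare the arms with the rank test that the Data analysis section already allows, and report medians with the number of such deaths per arm. An acceptable alternative is to analyse live extubation and live discharge as time-to-event outcomes with death as a competing event. The two answer different questions, so one should be chosen before unblinding.

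The cost is about one sentence in the endpoint definitions and a recode of the few deaths, with no new data, patients or visits. The downside is that the outcomes then combine duration with death and are summarised by ranks or medians, so the plain durations should still be reported descriptively.
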